## Abstract

**Background:**

Although clozapine is the most effective antipsychotic for people with treatment-resistant schizophrenia (TRS), only 40% of people with TRS respond, and there is limited evidence for augmentation agents. Cannabidiol (CBD) reduces positive symptoms in individuals with schizophrenia, but no trials have specifically examined its efficacy in those with clozapine-resistant schizophrenia.

**Aims:**

To examine the clinical efficacy of CBD augmentation in people with clozapine-resistant schizophrenia.

**Method:**

This is a 12-week randomised, placebo-controlled, double-blind, parallel-group trial (registration number: ACTRN12622001112752). We will recruit 88 individuals with clozapine-resistant schizophrenia, randomised (1:1) to 1000 mg daily CBD versus placebo. Eligible individuals will be aged between 18 and 64 years, fulfil DSM-IV criteria for schizophrenia or schizoaffective disorder, have a total PANSS (Positive and Negative Syndrome Scale) score ≥60, have received oral clozapine for at least 18 weeks and have a clozapine level of >350 ng/mL. Interim analyses will be conducted at 25, 50 and 75% recruitment; these will also provide an opportunity to reallocate participants dependent on conditional power. The primary endpoint will be the difference in PANSS positive scores at the end of week 12. Secondary endpoints include depression, anxiety, sleep, quality of life, alcohol consumption, change in weight and metabolic syndrome components, and neurocognitive measures, as well as safety and tolerability.

**Discussion:**

Novel treatments for clozapine-resistant schizophrenia are urgently needed. If found to be effective, CBD may have a role as a novel and safe adjunct to clozapine.

Schizophrenia, which is characterised by disturbances in cognition, affect, perception and behaviours, affects approximately 1% of the population;^1^ however, schizophrenia can be difficult to treat, even with optimal therapy. Roughly one-third of people with schizophrenia have treatment-resistant schizophrenia (TRS),^2^ defined as ongoing symptoms and functional impairment despite two adequate and adherent trials of different antipsychotics.^3^

Although antipsychotic medications and supportive therapies reduce symptom burden and relapse rate, many individuals with schizophrenia continue to have ongoing symptoms and concomitant cognitive and social disabilities, poor physical health and curtailed life expectancy.^4^ Currently, the most effective antipsychotic for TRS is clozapine, which leads to reductions in positive symptoms and hospital admissions.^5,6^ Even so, only 40% of people with TRS trialled on clozapine meet clinical response criteria.^7^ For people with clozapine-resistant schizophrenia, there are few agents available to augment treatment, and these have limited effectiveness.^8^

The endocannabinoid system has a strong neuromodulatory role, with effects on inflammation, cell proliferation and apoptosis, pain modulation, memory and learning, and fear, among other functions.^9^ Endocannabinoids bind to presynaptic receptors, including CB1 and CB2, to potentiate retrograde signals that regulate the release of other neurotransmitters, such as dopaminergic, serotonergic, adrenergic, cholinergic and γ-aminobutyric acid (GABA).^10,11^ Cannabidiol (CBD) is the non-intoxicating component of the cannabis plant. Compared with delta-9-tetrahydrocannabinol (THC), CBD has a more anxiolytic profile, sparing disturbances in perception and thought processing.^12^ CBD has strong potential for neuropsychiatric therapeutic use, as it acts on the central nervous system via neuroreceptors including CB1, the serotonin 5-HT1A receptor and the transient receptor potential vanilloid type 1 receptor.^13^ Recent studies have explored the potential of CBD to target the endocannabinoid system to improve mood and anxiety, epilepsy, chronic pain, movement disorders (such as Parkinson's disease), nausea and inflammation associated with metabolic syndrome, malignancy, atherosclerosis, etc.^11,13^ Following animal and *in vivo* studies, it has been suggested that CBD is non-toxic, with minimal (usually mild) side-effects.^14^ CBD has shown promise as a treatment for mental disorders, including anxiety, insomnia and post-traumatic stress disorder.^15^

There have been three randomised placebo-controlled trials, albeit not among people with clozapine-resistant schizophrenia.^16–18^ A 6-week double-blind parallel-group trial of 88 participants with partially responsive schizophrenia, not trialled on clozapine, compared adjunctive CBD 1000 mg/day with placebo.^17^ This study found significantly greater improvements in positive psychotic symptoms in the CBD group. However, it failed to reach significance with respect to the difference in the proportions of participants in the two groups showing ≥20% improvement in PANSS (Positive and Negative Syndrome Scale) total score. A second 4-week blind randomised controlled trial (RCT) among 42 participants receiving 600–800 mg CBD daily versus the standard antipsychotic medication, amisulpride, showed improvements in psychotic symptoms with both treatments and fewer adverse drug reactions in the CBD arm.^18^ However, the third study, a double-blind 6-week randomised controlled trial in 36 treatment-responsive patients with schizophrenia did not find a difference in psychotic symptoms between groups receiving adjunctive CBD 600 mg/day and placebo.^16^ Other non-randomised or single-dose CBD studies have shown equivocal results.^19^

CBD has been found to be well tolerated at different doses across several clinical trials. A trial by Taylor et al in healthy controls showed good tolerance of single CBD doses of 1500, 3000, 4500 and 6000 mg.^20^ In patients receiving multiple doses (750 and 1500 mg twice daily) for 6 days, CBD was also well tolerated, with no participants leaving the trial owing to adverse events.^20^ McGuire et al trialled doses of 1000 mg daily of CBD in patients with schizophrenia in addition to their usual antipsychotic medications for 6 weeks.^17^ Positive psychotic symptoms were lower in the treatment group, with similar adverse events to those of the placebo group, showing good tolerance for CBD.^17^

To date, there have been no trials of CBD among people with clozapine-resistant schizophrenia. This trial has the potential to identify CBD – if found to be effective – as a novel and safe adjunctive treatment for individuals with clozapine-resistant schizophrenia.

## Study objectives

The aim of this study is to examine the clinical efficacy of an add-on CBD treatment in patients with clozapine-resistant schizophrenia. The primary objective is to determine the impact of 12-week treatment with CBD, compared with placebo, on scores on the positive subscale of PANSS in patients with clozapine-resistant schizophrenia.

## Hypothesis

We hypothesise that participants allocated to the intervention group (1000 mg daily CBD treatment) will demonstrate a reduction in PANSS positive scores at the end of week 12 compared with participants receiving placebo.

## Method

### Design and setting

The study is a randomised, placebo-controlled, double-blind parallel-group adaptive trial to examine the clinical efficacy and safety of add-on CBD treatment in patients with clozapine-resistant schizophrenia. It will recruit 88 individuals with clozapine-resistant schizophrenia, who will be randomised at the point of providing written informed consent. The study design was discussed with our local lived experience reference group.

Participants will be given 1000 mg daily of CBD or placebo, in addition to routine care. A battery of validated clinical and physical health measures will be conducted throughout the trial period. Adverse events will be recorded fortnightly (i.e. weeks 0, 2, 4, 6, 8, 10 and 12), and trial medication will be distributed to participants fortnightly (i.e. weeks 0, 2, 4, 6, 8 and 10).

The authors assert that this study complies with the ethical standards of the relevant national and institutional committees on human experimentation and with the World Medical Association Declaration of Helsinki *Ethical Principles for Medical Research Involving Human Subjects*.^21^ All procedures involving human participants were approved by the Metro South Human Research Ethics Committee (reference number: HREC/2022/QMS/83530). The study sponsor is the University of Queensland, which provides overarching governance. We have separate site governance approvals for each recruiting site. The trial is registered on the Australia New Zealand Clinical Trials Registry (registration number: ACTRN12622001112752). The study will follow the CONSORT guidelines for parallel-group randomised trials.^22^

### Participants

Eighty-eight eligible participants with TRS will be recruited through mental health services at the Gold Coast, Metro North, Metro South, and West Moreton Hospital and Health Services and in south-east Queensland, Australia. Participant eligibility is detailed in Box 1. Participants must meet all the inclusion criteria and none of the exclusion criteria. Capacity to consent will be determined by the treating clinician in collaboration with clinical trial staff. Only participants with this capacity will be recruited following their provision of consent.
Box 1Participant eligibility**Table d67e567:** 

Inclusion criteria
Individuals will be invited to participate in the study if they meet all the following criteria:
(a) aged between 18 and 64 years (inclusive);
(b) meet DSM-IV criteria for schizophrenia or schizoaffective disorder, based on the Diagnostic Interview for Psychoses^23^;
(c) have clozapine-resistant schizophrenia as defined by total Positive and Negative Syndrome Scale score ≥60;
(d) have received oral clozapine for a period of ≥18 weeks, with a clozapine level of >350 ng/mL;
(e) agree to participate in the trial, have the capacity to consent, and can follow study instructions and procedures.
Exclusion criteria
Individuals will not be invited to participate in the study if they meet any of the following criteria:
(a) are currently pregnant, lactating, or not using effective contraception if sexually active (applicable to both male and female patients);
(b) present clinical blood test results that might compromise patient safety or confound trial results;
(c) are currently using psychotogenic substances including amphetamine and cannabis (by self report);
(d) are actively using other prescribed cannabinoids;
(e) are experiencing severe disturbance, such that the person is unable to comply with either the requirements of informed consent or the treatment protocol;
(f) have any concomitant disease or condition that according to the investigator's assessment makes the patient unsuitable for trial participation;
(g) have ceased using clozapine.

### Allocation concealment and randomisation

Participants will be randomised using a chronological process and only after written consent has been provided and baseline assessments have been completed. Participants will be randomised to either the intervention or control group in a 1:1 ratio using a computer-generated randomisation table with block randomisation. They will be allocated a unique identification number, which will be linked to a specific number based on the site they have been recruited from. If a participant withdraws from the study, their identification number will not be re-used, nor will they be allowed to re-enter the study.

Participants, clinical trial staff, investigators and treating clinicians will be blinded to the intervention. An independent biostatistician will generate the randomisation list, which will be provided to the manufacturer and a study site pharmacist. The pharmacist will hold the closed randomisation list and will be the only one who is able to unblind participants. In the case of an emergency, where it is critical that medical staff know whether a participant is on CBD or placebo, participants will be provided with contact information for unblinding (i.e. a 24-h number).

### Pharmacological treatment

Participants will receive five gel capsules per day containing either 200 mg CBD (99% purity; <0.1 mg THC per capsule) suspended in medium-chain triglyceride oil or matched placebo (medium-chain triglyceride oil only). Capsules were manufactured by Linnea SA, Lavertezzo, Switzerland, a Therapeutic Goods Administration licensed facility, in accordance with current Good Manufacturing Practice and distributed by BOD Science. Dispensation, by a clinical trial staff member, will occur on a fortnightly basis, with six dispensations total per participant.

### Outcomes

#### Primary

The primary outcome was the impact of 1000 mg daily CBD treatment over 12 weeks compared with placebo on PANSS positive score in participants with clozapine-resistant schizophrenia.

#### Secondary

Secondary outcomes included the impact of 1000 mg daily CBD treatment over 12 weeks compared with placebo on PANSS total scores and other PANSS subscales; depression; anxiety; sleep; quality of life; alcohol consumption; changes in weight and metabolic syndrome components including waist circumference, haemoglobin A1C (HbA1c), high-density lipoprotein (HDL), low-density lipoprotein (LDL), body mass index (BMI), triglycerides, blood pressure, hip-to-waist ratio, electrolyte and liver function tests (ELFTs), non-alcoholic fatty liver disease (NAFLD) scores, fibrosis-4 scores (FIB-4), heart rate, diet and appetite, and physical activity; endpoint clozapine and norclozapine levels compared with baseline; and neurocognitive measures. Additional aims were to determine the safety and tolerability over 12 weeks of 1000 mg daily CBD in patients with clozapine-resistant schizophrenia compared with placebo as measured by the number of participants reported to have dropped out, number of adverse events reported, and scores from a structured qualitative interview with participants about their experience with the study investigational product using the Systematic Assessment for Treatment Emergent Events – Systematic Inquiry (SAFTEE-SI).^24^

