#### Participant safety

To assess the preliminary safety and tolerability of 1000 mg daily CBD for 12 weeks in people with clozapine-resistant schizophrenia (secondary objective), we will assess:
the dropout rate between intervention and control groups;the numbers of adverse events reported in the intervention and control groups;liver function test results at baseline and weeks 6 and 12;scores from a structured qualitative interview with participants about their experience with the trial investigational product using the SAFTEE-SI.

All participants will be currently active cases across Queensland Hospital and Health Services. The research team will communicate with clinicians to guarantee that all participants have undergone a regular biannual physical health assessment as part of their standard care. The investigator and clinical trial staff will oversee any adverse events reported during the study. Any adverse events reported between participant consent and final follow-up will be recorded using designated case report forms.

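### Tolerability is measured by dropout of any cause and by adverse-event totals; the first can hide withdrawals due to side-effects, and the second can be biased in either direction

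*Protocol article*

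**What the plan says.** Outcomes – Secondary names three measures of safety and tolerability. Two are the "number of participants reported to have dropped out, number of adverse events reported". The third is "scores from a structured qualitative interview with participants about their experience with the study investigational product", collected with the SAFTEE-SI.

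The Participant safety section lists the same measures by arm: "the dropout rate between intervention and control groups" and "the numbers of adverse events reported in the intervention and control groups", with the SAFTEE-SI again. It adds "liver function test results at baseline and weeks 6 and 12". Table 1 has a row for dropouts under Safety, marked once, at week 12. It schedules adverse events and the SAFTEE-SI at every visit from week 0 to week 12.

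On collection, Design and setting states: "Adverse events will be recorded fortnightly". Participant safety gives the window: "Any adverse events reported between participant consent and final follow-up will be recorded using designated case report forms". Table 1 places consent at screening and the first supply of capsules at week 0.

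None of these places splits dropout by reason or gives a denominator for adverse events (participants or exposure time). The term all-cause does not appear, but no cause is named.

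**The concern.** The trial compares a drug that its investigators expect to work with placebo. In that setting people leave for at least two reasons: lack of benefit, which would be commoner on placebo if CBD works, and intolerance, which would be commoner on CBD if it has side-effects. A dropout count that ignores cause adds the two together. They can cancel, and the arms then look equally well tolerated although more people stopped CBD because of side-effects.

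The number of adverse events has a different weakness. Someone who leaves the study early has fewer fortnightly visits at which to report anything, so an arm's total depends on how long its members stay. The window also opens at consent, so the total as worded can include events that occurred before any capsule was taken.

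The article hopes to identify CBD as a safe adjunct to clozapine. With 44 people per arm, a handful of adverse-event withdrawals would bear on that conclusion and could be lost in an undivided total.

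**Working it through.** **The plan's own figure.** The Sample size section starts from 70 participants and allows for 20% dropout: 70 / (1 − 0.20) = 87.5, rounded up to 88. This reproduces. With 1:1 allocation it gives 44 per arm, and 20% of 44 is 8.8, or about 9 dropouts per arm. The article gives no split of dropout by arm or by cause, so every split below is an assumption.

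**Step 1: dropout by cause.** Suppose 9 people leave each arm.

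| | CBD (n = 44) | Placebo (n = 44) | Fisher exact P |
|---|---|---|---|
| All dropouts | 9 (20%) | 9 (20%) | 1.00 |
| Because of an adverse event | 7 (16%) | 1 (2%) | 0.058 |
| Lack of benefit | 2 | 8 | – |

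The stated measure shows no difference, while the cause-specific one shows 7 v 1. A milder assumed split of the same totals (6 v 1 for adverse events) gives P = 0.11.

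**Step 2: adverse-event totals at equal true rates.** Person-weeks per arm = 44 × [(1 − d) × 12 + d × t], where d is the proportion leaving the study and t the week of leaving. If both arms have the same event rate per week and reporting ends on leaving, the ratio of expected totals equals the ratio of person-weeks.

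| Dropout, CBD v placebo | Week of leaving | Person-weeks, CBD v placebo | Ratio of totals, CBD/placebo |
|---|---|---|---|
| 10% v 30% | 6 | 501.6 v 448.8 | 1.12 |
| 10% v 30% | 2 | 484.0 v 396.0 | 1.22 |
| 15% v 25% | 6 | 488.4 v 462.0 | 1.06 |
| 15% v 25% | 2 | 462.0 v 418.0 | 1.11 |
| 30% v 10% | 6 | 448.8 v 501.6 | 0.89 |
| 30% v 10% | 2 | 396.0 v 484.0 | 0.82 |

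When placebo loses more people, the totals make CBD look worse than it is. When CBD loses more, they make it look better.

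**Step 3: would the dropout rate reveal the second case?** With 30% v 10% dropout, the counts are about 13 v 4 of 44 (P = 0.029). With 40% v 10%, they are about 18 v 4 (P = 0.001). So where event totals flatter CBD noticeably, the dropout rate by arm would itself show the imbalance.

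**Step 4: events before the first capsule.** Consent is at screening and capsules start at week 0. A count that runs from consent therefore covers an untreated interval in both arms. Such events say nothing about CBD and dilute the comparison.

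**The case against.** The strongest reply is that this is a condensed article. Reasons for withdrawal, the definition of treatment-emergent events, denominators and person-time are often left to the full protocol or analysis plan, which are not shown, and the fields of the case report forms are not shown either. That is right as far as missing detail goes, and the article does not say that reasons will go unrecorded. It does not remove the point, because dropout and the number of events are named as the measures in Outcomes – Secondary, in Participant safety and, for dropout, in the Safety rows of Table 1. A later document could add reasons, but the named outcome would remain undivided dropout.

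Other parts of the reply stand:

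- **The measures are reported together.** The SAFTEE-SI is asked at every visit and liver function is tested at baseline and weeks 6 and 12. The events that lead someone to leave should also be recorded as adverse events. Neither the SAFTEE-SI nor liver testing identifies who stopped because of side-effects, however, and visit-based SAFTEE-SI scores are lost once a participant leaves.
- **Stopping capsules need not end event recording.** Events are recorded to final follow-up, so the bias in totals arises from leaving the study.
- **The assessment is called preliminary**, and no test or decision rule for tolerability is stated.

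A reader might infer that both measures favour an effective CBD arm. The documents do not support that: placebo loss that flatters CBD on dropout works against CBD on event totals. A reader might also infer that one person's recurring complaint is counted repeatedly, but no counting rule is given. Nor does the introduction's phrase "no participants leaving the trial owing to adverse events" set a yardstick for this trial. It describes one cited study with 6 days of repeated dosing, and the same paragraph judges another trial by its similarity to placebo in adverse events.

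**Conclusion.** The point holds in a limited form. Dropout without regard to cause is a poor measure of tolerability in a placebo-controlled efficacy trial, because equal totals can conceal an excess of adverse-event withdrawals on CBD. Event totals depend on time in the study and, as worded, include the period before first dose; unequal dropout can bias them either way.

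The size is unknown. The 7 v 1 split and the ratios of 0.82 to 1.22 rest on assumed dropout by arm and cause, on the assumed week of leaving and, for the ratios, on equal event rates with reporting that ends when a participant leaves. They show what is possible, not what is likely. It does not follow that the trial would wrongly declare CBD well tolerated: the measures are read together, and a large excess of CBD dropout would be visible. The change is worth making because it is cheap and because reasons not captured when someone stops may not be recoverable later.

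**What to change.** 1. Record the reason when a participant stops capsules or leaves the study, before unblinding.
2. Add discontinuation because of an adverse event, by arm, as a tolerability outcome in Outcomes – Secondary and Participant safety. Keep all-cause dropout as a description of participant disposition.
3. Report adverse events as the number of participants with at least one new or worsened event after first dose, with events per person-week as support, in place of raw totals alone. List events between consent and first dose separately.
4. Keep the SAFTEE-SI and liver tests as planned.

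If the full protocol or analysis plan already does this, aligning the wording of the outcomes is enough. Otherwise the cost is one form field and one extra table, with no new visits or procedures. The downside is that attributing a reason involves some judgement, although it would be made blind to treatment.

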#### Tertiary

Tertiary outcomes were changes between baseline and the 12-week endpoint in CBD and CBD metabolites (7-COOH-CBD, 6-OH-CBD, 7-OH-CBD), medication adherence, and measurements of THC and its metabolites (11-COOH-THC, 11-OH-THC) to check for possible illicit cannabis use.

